### Statistical analysis

All statistical analyses will be performed using SPSS version 28.0 (IBM Corporation, Armonk, NY, USA). Descriptive statistics will be used to summarize baseline participant characteristics in each group. Continuous variables (e.g., age, BMI, percentage body fat) will be presented as means and standard deviations, while categorical variables (e.g., sex, group allocation) will be presented as frequencies and percentages.

The primary outcome measure is the MRI-derived MFR. The primary analysis will focus on the between-group difference in change in MFR at the post-intervention assessment (week 16); this is the primary outcome indicator for the trial. The 6-month follow-up assessment will be included to examine the maintenance of intervention effects over time. Generalized estimating equations (GEE) will be used to account for within-subject correlation across the two post-baseline assessments (post-intervention at 16 weeks and 6-month follow-up). The intervention group will be treated as a three-level categorical variable, with the HE control group as the reference. Time will be specified as a categorical variable. Group, time, and group-by-time interaction will be included in the model. Baseline MFR values, age, and sex will be included as covariates. An exchangeable working correlation structure will be specified, with robust sandwich standard errors used for estimation. Pairwise comparisons will be performed to compare Plyo-HIIT with SF and HE at week 16. Sensitivity analyses using a different working correlation structure will also be performed.

Secondary outcomes, including percentage body fat, muscular strength, muscular endurance, muscular power, cardiorespiratory fitness, flexibility, BMI, physical activity level, and cortisol levels, will be analyzed similarly using a GEE model. For each secondary outcome, the corresponding baseline value will be included as a covariate where appropriate. These analyses will be considered exploratory.

All analyses will follow the intention-to-treat principle, including all randomized participants regardless of adherence. Missing data will be processed using multiple imputation methods to minimize bias as much as possible. A per-protocol sensitivity analysis will also be performed including only participants with at least 80% attendance in intervention sessions. Effect estimates will be reported with 95% confidence intervals where appropriate. For the prespecified primary pairwise comparisons, the significance level will follow the adjustment described in the sample size calculation. For exploratory secondary analyses, a two-sided *P* value < 0.05 will be considered statistically significant.

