### Randomization and blinding

Participants will be randomly assigned to one of the three study groups (Plyo-HIIT, SF program, or HE control) using a computer-generated randomization list with randomly permuted block sizes of 3 and 6 to achieve a 1:1:1 allocation ratio (Fig. 1). The allocation sequence will be generated by an independent researcher who is not involved in recruitment, assessment, or intervention delivery to prevent allocation bias. Group allocation will be concealed using sealed, opaque, and consecutively numbered envelopes prepared by an independent researcher to ensure allocation concealment until the point of assignment.

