### Interventions

This study consists of three intervention groups: Plyo-HIIT, SF program, and HE control group. All interventions will be delivered over a 16-week period, with two 45-minute sessions per week during school-arranged after-school activity periods at participating schools. To support adherence and minimize loss to follow-up within a school-based setting, sessions will be scheduled as part of regular school activities and delivered in groups, with attendance recorded throughout the intervention period. The SF and Plyo-HIIT interventions will be delivered by two to three trained instructors who have completed a standardized training session. Intervention fidelity will be maintained through standardized instructor training, class video recordings, and biweekly on-site monitoring by researchers to verify protocol delivery and provide feedback when needed.

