## Results

This protocol describes an ongoing randomized controlled trial registered in the Chinese Clinical Trial Registry (ChiCTR2500110770). Participant recruitment took place between September 26, 2024 and March 14, 2025. The 16-week intervention has been completed. However, as one participating cohort delayed the start date of the intervention, the 6-month follow-up assessments are still ongoing, with the final follow-up assessment scheduled for August 2026. Data cleaning is being conducted for completed assessments, and final outcome analysis will be performed after completion of the remaining follow-up assessment. Therefore, no trial outcome data are reported in this protocol article.

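### The primary GEE models correlation within the child only; if outcomes also correlate within the session groups that deliver treatment, the nominal 1% level is exceeded

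*Protocol article*

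**What the plan says.** **Allocation.** Under Randomization and blinding, individual children are allocated "using a computer-generated randomization list with randomly permuted block sizes of 3 and 6 to achieve a 1:1:1 allocation ratio".

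**Delivery.** Under Interventions, all three arms run twice weekly for 16 weeks at participating schools: "sessions will be scheduled as part of regular school activities and delivered in groups". For the two exercise arms, "The SF and Plyo-HIIT interventions will be delivered by two to three trained instructors who have completed a standardized training session". The HE arm is taught by researchers, also to small groups.

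**Primary model.** Under Statistical analysis: "Generalized estimating equations (GEE) will be used to account for within-subject correlation across the two post-baseline assessments". The model has group, time and their interaction. On covariates it says "Baseline MFR values, age, and sex will be included as covariates", and on estimation "An exchangeable working correlation structure will be specified, with robust sandwich standard errors used for estimation". The only model sensitivity analysis named there is a different working correlation structure.

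**Error level.** The primary pairwise comparisons are sent back to the Sample size section for their significance level. The only level given there is 0.01.

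**Elsewhere.** The Sample size section has no ICC or design effect, and the limitations in the Discussion do not mention clustering.

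**The concern.** This is an individually randomised trial with group-delivered treatment. The three programmes differ in content, so each session group belongs to one arm. Children in a group share sessions, leaders and peers. In Plyo-HIIT the instructors may also vary repetitions and rest, and the Discussion accepts that school schedules and motivation can affect adherence. Any resulting group effect does not cancel in the comparison of arms: it adds variance to the difference between arm means.

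A sandwich estimator protects against correlation inside the declared cluster and assumes independence between clusters. Here the cluster is the child. Changing the working correlation, as the planned sensitivity analysis does, still treats children as independent.

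At stake are the standard errors, confidence intervals and 1% error rate of both primary contrasts. Secondary outcomes use the same type of model and inherit the problem.

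**Working it through.** **1. The plan's own figure.** Inputs from Sample size: 3 groups (k), 3 measurements (m), f = 0.22, correlation 0.2, ε = 0.70, α = 0.01, power 90%. For the within-between interaction:

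- λ = f²·N·m·ε/(1 − ρ) = 0.0484 × 153 × 3 × 0.70/0.80 = 19.44
- df1 = (k − 1)(m − 1)ε = 2 × 2 × 0.70 = 2.8
- df2 = (N − k)(m − 1)ε = 150 × 2 × 0.70 = 210

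Power is 0.9004, so N = 153 reproduces, and 153/0.75 = 204. Both figures treat children as independent.

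**2. Error of the planned test under clustering.** Assumed, because the documents give neither: g children per session group (5 to 25) and a session-group ICC (0.01 to 0.10).

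- Design effect: DE = 1 + (g − 1) × ICC
- True SE / model SE = √DE
- Actual two-sided error of a nominal 1% test = 2 × [1 − Φ(2.576/√DE)]

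Example with g = 10 and ICC = 0.05: DE = 1 + 9 × 0.05 = 1.45; √DE = 1.20; actual error 3.2%.

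| g | ICC 0.01 | ICC 0.02 | ICC 0.05 | ICC 0.10 |
|---|---|---|---|---|
| 5 | 1.2% | 1.3% | 1.9% | 3.0% |
| 10 | 1.4% | 1.8% | 3.2% | 6.2% |
| 15 | 1.6% | 2.3% | 4.8% | 9.6% |
| 20 | 1.8% | 2.8% | 6.5% | 13.0% |
| 25 | 2.1% | 3.4% | 8.3% | 16.2% |

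The SE ratio runs from 1.02 (g = 5, ICC 0.01) to 1.84 (g = 25, ICC 0.10). At ICC = 0 the 1% level stands.

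**3. Simulation check.** 20,000 runs of a two-arm comparison of means at one time point, tested as if children were independent. This is simpler than the planned GEE but has the same fault. With 5 groups of 10 per arm, rejection under the null was 2.0%, 3.6% and 6.9% at group ICC 0.02, 0.05 and 0.10. With no clustering it was 1.1%.

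**4. Which level causes it.** In the same simulation, school effects shared by both arms, with no session-group effect, gave about 0.8% to 1.0%: no inflation. With school and group ICC both 0.05 (5 groups of 10 per arm) the error was 3.5%, against 3.6% with the group effect alone. The source is the group nested in arm, not the school.

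**5. Information.** Taking effective N = 153/DE as an approximation, at g = 10 and ICC 0.05 it is 153/1.45 ≈ 106, and the power of the planned F test falls from 90.0% to 70.9%.

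**The case against.** The strongest reply is that nothing shows the ICC to be appreciable. The outcome is an MRI measure read by blinded staff. Delivery is standardised through instructor training, video recording and on-site monitoring every two weeks, which should limit differences between groups. HE is taught to small groups, and after attrition the plan counts on 153/3 = 51 children per arm, so 10 per group is easier to defend than 15 or more. With 5 per group and ICC 0.01 the error is 1.2%, which is negligible. Even 15 per group with ICC 0.02 gives 2.3%, below the 2.5% of a 5% level split over two contrasts.

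That argument stands as to size: how far the level is exceeded is unknown and could be slight. It does not remove the mismatch between delivery and model, and at 10 per group with ICC 0.05 the error (3.2%) is above 2.5% as well. A separate analysis plan might handle clustering, but the article sets out the primary model in detail and names only one level of correlation.

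A reader might infer more than the documents support:

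- *That leaving out school or start cohort inflates the error.* It does not when children are randomised individually (step 4). The Results section reports that "as one participating cohort delayed the start date of the intervention", but this bears on precision, and the article does not equate cohort with school.
- *That every arm is led by a handful of instructors.* Two to three are stated for SF and Plyo-HIIT only. Whether the same people lead both is not said; if they do, instructor is crossed with arm in that contrast.
- *That a group identifier is already on file.* The article says only that attendance is recorded.

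**Conclusion.** The point holds in conditional form. The stated primary model omits a level of correlation that the trial's own delivery creates, and nothing else in the article makes up for it. If the session-group ICC is above zero, both primary standard errors are too small and the 1% level is exceeded.

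The size rests entirely on an assumed ICC and group size, equal groups and a normal approximation. It cannot be said that the error rate will fail by a given amount, only that the plan offers no protection if children taught together resemble one another. Because this concerns both primary tests, and the Results section says the final outcome analysis is still to come, it should be settled before that analysis is run.

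**What to change.** Amend the primary model before the final analysis to include the session group (school-by-arm delivery group). Either:

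- fit a linear mixed model with a random session-group effect, repeated measures within child, and Satterthwaite or Kenward-Roger degrees of freedom; or
- keep GEE, define the cluster as the session group, and use a small-sample-corrected sandwich.

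Report the estimated session-group ICC and the number and size of groups. First confirm that each child's group membership was recorded, and that the named software offers the chosen correction. School or start cohort may be added as a fixed factor for precision, but not in place of the session-group term.

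**Cost.** A change of model wording and one identifier per child; no new outcome data. Intervals will be wider and degrees of freedom fewer, the more so with few groups. In a layout of 5 groups per arm, for instance, the group-level degrees of freedom are 3 × 5 − 3 = 12, and the two-sided 1% critical value rises from 2.58 to about 3.05. If the groups prove very few, that limit should be stated alongside the result.

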### Sample size

Sample size was calculated based on the primary outcome, MRI-derived MFR, using a repeated-measures analysis including baseline, post-intervention, and 6-month follow-up measurements. The primary endpoint is the between-group difference at the post-intervention assessment (week 16), with the 6-month follow-up included to evaluate maintenance of intervention effects over time.

A power analysis was conducted using G*Power 3.1 (*F* test, repeated-measures ANOVA, within-between interaction; 3 groups × 3 measurements). As no prior randomized controlled trials have examined MRI-derived MFR changes in children following Plyo-HIIT, an effect size specific to MFR is currently unavailable. Therefore, the expected effect size will be estimated based on pediatric exercise intervention studies reporting changes in BMI-related adiposity outcomes, which are conceptually related to body composition adaptations.

A previous study reported a mean between-group difference of 0.2 in BMI *Z* score, with a standard deviation (SD) of 0.45, corresponding to Cohen’s *d* ≈ 0.44 [53]. This was converted to an ANOVA effect size of *f* = 0.22 and used as a conservative proxy for the primary outcome. This approach was adopted to avoid underestimating the required sample size in the absence of directly comparable MFR intervention data.

To adopt a stringent and conservative design strategy, the significance level was set at *α* = 0.01. Statistical power was set at 90% to ensure adequate sensitivity for detecting clinically meaningful intervention effects over time.

Given the 16-week and 6-month follow-ups, a conservative assumption was made for the correlation among repeated measures (*r* = 0.2) to avoid overestimating within-subject stability across extended time intervals. The Greenhouse–Geisser nonsphericity correction was set to *ε* = 0.70, reflecting possible variability and differences between time intervals.

With these assumptions, the analysis indicated that a total of 153 participants is required. To accommodate an estimated 25% attrition rate, the minimum sample size was set at 204. To further ensure adequate power for subgroup and sensitivity analyses, and to allow for potential uneven group sizes after attrition, the recruitment target was rounded up to 210 participants (70 per group).

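### The primary GEE gives baseline MFR one slope shared by weeks 16 and 42; adding baseline MFR × time would protect the precision of the week-16 contrast at almost no cost

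*Protocol article*

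**What the plan says.** The Statistical analysis section of the Protocol article places the primary comparison at week 16 and uses week 42 to look at maintenance. Both post-baseline visits form the outcome vector of a single GEE. The terms are listed: "Group, time, and group-by-time interaction will be included in the model". Time is categorical and group has three levels. On adjustment the text says "Baseline MFR values, age, and sex will be included as covariates". On estimation it says "An exchangeable working correlation structure will be specified, with robust sandwich standard errors used for estimation". The one stated sensitivity analysis of the model is this: "Sensitivity analyses using a different working correlation structure will also be performed".

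No covariate-by-time term is stated, and none is expressly excluded. Because the terms are listed and only one interaction is among them, the plain reading is one coefficient per covariate, common to both visits.

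The Sample size section assumes a single correlation of 0.2 for all pairs of visits. It adds a nonsphericity correction of 0.70, described as "reflecting possible variability and differences between time intervals".

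**The concern.** The model lets the group effect differ by visit but not the effect of baseline MFR. Week 42 is 42/16 ≈ 2.6 times as far from baseline as week 16, and it follows 26 weeks without intervention in children aged 9–12. It is plausible that baseline MFR predicts the two visits differently. If so, a shared slope is not the best slope for week 16, and the only primary endpoint is adjusted partly with information about week 42. Some baseline variation that the trial has measured, and could remove, would then stay in the primary contrasts. What is at stake is the width of the confidence interval and some power, not the correctness of the estimate.

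**Working it through.** **1. The plan's own figure.** Inputs from Sample size: f = 0.22, α = 0.01, power 90%, 3 groups, 3 measurements, r = 0.2, ε = 0.70. The noncentrality is f²·N·m·ε/(1−r) = 0.0484 × 153 × 3 × 0.70/0.8 = 19.44, with df 2 × 2 × 0.70 = 2.8 and 150 × 2 × 0.70 = 210. Power is 0.8979 at N = 152 and 0.9004 at N = 153, so 153 reproduces, and 153/0.75 = 204. The calculation contains no separate correlations of baseline with week 16 and with week 42, so it does not settle the point.

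**2. Which slope is used.** Let b16 and b42 be the slopes of each visit on baseline MFR. With complete data, a baseline value constant over visits and an exchangeable working correlation, the two visits receive equal weight. The common slope is therefore b̄ = (b16 + b42)/2. The week-16 contrast is the difference in week-16 means minus b̄ times the difference in baseline means. With two visits a working correlation matrix has a single off-diagonal value, so the planned sensitivity analysis does not free the slopes.

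**3. Cost at week 16.** Take SD 1 at baseline and week 16, so that b16 = r16 and b42 = r42 × (SD at week 42).

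- Residual variance with its own slope: 1 − r16²
- Residual variance with the shared slope: 1 − r16² + ((b16 − b42)/2)²

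All correlations below are assumptions, except that 0.2/0.2 uses the protocol's single value.

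| r16 / r42 | SD at week 42 | Added term / own-slope variance | Excess variance |
|---|---|---|---|
| 0.2 / 0.2 | 1 | 0 / 0.96 | 0% |
| 0.3 / 0.1 | 1 | 0.01 / 0.91 | 1.1% |
| 0.8 / 0.7 | 1 | 0.0025 / 0.36 | 0.7% |
| 0.9 / 0.8 | 1 | 0.0025 / 0.19 | 1.3% |
| 0.8 / 0.6 | 1 | 0.01 / 0.36 | 2.8% |
| 0.9 / 0.7 | 1 | 0.01 / 0.19 | 5.3% |
| 0.8 / 0.4 | 1 | 0.04 / 0.36 | 11.1% |
| 0.9 / 0.6 | 1 | 0.0225 / 0.19 | 11.8% |
| 0.9 / 0.5 | 1 | 0.04 / 0.19 | 21.1% |
| 0.9 / 0.9 | 1.2 | 0.0081 / 0.19 | 4.3% |
| 0.8 / 0.6 | 1.33 | about 0 / 0.36 | 0% |

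The last two rows show that slopes matter, not correlations alone. Equal correlations can cost precision if the spread grows, and falling correlations can cost nothing.

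**4. Simulation.** The exchangeable GEE with sandwich errors was fitted with and without baseline × time (N = 153, 2,000 runs per scenario, no missing data). Variance ratios at week 16 were 0.999 (0.2/0.2), 1.023 (0.8/0.6), 1.048 (0.9/0.7), 1.115 (0.8/0.4) and 1.049 (0.9/0.9 with SD 1.2), in line with the formula. Neither model showed bias. At 0.2/0.2 the extra term had essentially no cost.

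**5. Scale in power.** With 153/3 = 51 per arm, d = 0.44 and two-sided α = 0.01, power = Φ(0.44/(σ√(2/51)) − 2.576).

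- 0.8/0.6: σ² rises from 0.36 to 0.37, and power falls from 0.870 to 0.859.
- 0.8/0.4: σ² rises from 0.36 to 0.40, and power falls from 0.870 to 0.826.
- 0.9/0.7: σ² rises from 0.19 to 0.20, and power falls from 0.994 to 0.992.

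**The case against.** The strongest reply is that nothing here is wrong. Baseline as a main effect in a longitudinal GEE is common and acceptable, and the estimate and its standard error remain valid. The article condenses a fuller plan, and a covariate-by-time term could sit there. The only correlation in the documents is one value of 0.2, under which the loss is zero with equal SDs. Near that level even decay costs little (1.1% of variance at 0.3/0.1). Every larger figure rests on assumed correlations.

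Most of this stands, and it sets the weight of the point. It does not remove the point. The section lists its terms and names one interaction, so a shared slope is what the stated model contains, not merely an unmentioned detail. The protocol also presents 0.2 as a cautious choice, so it is not a forecast of equal, low correlations.

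A reader might infer from ε = 0.70 that the plan itself expects baseline to predict the two visits differently. The documents do not support that. Some decay patterns do give values near 0.70: for baseline–16/baseline–42/16–42 correlations, 0.9/0.7/0.8 gives 0.75 and 0.9/0.6/0.8 gives 0.64. But 0.2/0.2/0.79 gives about 0.70 with equal slopes, so ε does not fix the slopes.

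A reader might also object that the primary estimate moves with week-42 data. The Results section places the final outcome analysis after the remaining follow-up, so no earlier week-16 analysis is disturbed.

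**Conclusion.** The point holds as a minor efficiency improvement. As written, the week-16 contrast is adjusted with the average of the week-16 and week-42 baseline slopes. The excess variance is zero with equal slopes and about 1–5% under moderate decay in correlation (SE about 0.3% to 2.6% larger). It is about 11–12% or more only under steep decay. These figures assume complete data and correlations that the documents do not give; dropout or imputation would shift the weights of the two slopes.

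Three stronger readings are not supported:

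- **That precision is certainly lost.** This depends on unequal slopes, which the documents neither state nor imply.
- **That chance baseline imbalance is under-corrected at week 16.** This holds only if the week-42 slope is the smaller one. If it is larger, the shared slope over-corrects. Either way the effect averages out over randomizations.
- **That the shared age and sex coefficients cause a comparable loss.** The mechanism is the same, but its size was not quantified.

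**What to change.** In Statistical analysis, state the primary model as group, time, group × time, baseline MFR, baseline MFR × time, age and sex. Week 16 then has its own baseline slope. Age × time and sex × time may be added; with all three, the week-16 contrast on completed data equals the week-16 covariate-adjusted comparison. If the sponsor prefers the present model, say explicitly that the covariate slopes are assumed common to both visits.

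The cost is one line of wording and one to three nuisance parameters with a target of 210 children. No new data are needed. The final outcome analysis is still pending according to the Results section, so the change can be fixed beforehand. The exploratory secondary outcomes can follow the same form for consistency, but little depends on it.

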## Methods

### Study hypothesis and purpose

This study aimed to investigate the effectiveness of a 16-week school-based Plyo-HIIT intervention in improving MFR among children aged 9–12 years. Specifically, the study compares the outcomes of a Plyo-HIIT program with the SF program and the HE control group. The primary hypothesis is that children allocated to the Plyo-HIIT group will demonstrate greater improvements in MRI-derived MFR compared with the SF and HE groups immediately following the intervention (week 16). The 6-month follow-up assessment (week 42) is included to examine whether intervention effects are maintained over time. In addition, the study will examine intervention-related changes in InBody-derived body fat percentage, muscular strength, endurance and power, cardiorespiratory fitness, flexibility, physical activity levels, body mass index (BMI), and physiological stress, indicated by hair cortisol levels.

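### The stated 90% power belongs to a three-visit interaction test; for the primary week-16 pairwise comparisons the plan's own inputs give about 37%

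*Protocol article*

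**What the plan says.** The hypothesis section, the primary outcome section, the sample size section and the statistical analysis section all put the primary question at week 16. The hypothesis names both comparators. The statistical analysis section says: "Pairwise comparisons will be performed to compare Plyo-HIIT with SF and HE at week 16". These contrasts come from a GEE model whose responses are the two post-baseline visits; baseline MFR, age and sex are covariates. On the significance level it says: "For the prespecified primary pairwise comparisons, the significance level will follow the adjustment described in the sample size calculation". The only level given in the sample size section is this: "the significance level was set at *α* = 0.01".

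The sample size section, however, powers "repeated-measures ANOVA, within-between interaction; 3 groups × 3 measurements". It takes a between-group difference of 0.2 in BMI Z score with SD 0.45 (d about 0.44), converts this to f = 0.22, and assumes a correlation of 0.2 and a nonsphericity correction of 0.70. On power it says: "Statistical power was set at 90% to ensure adequate sensitivity for detecting clinically meaningful intervention effects over time". The result is 153 evaluable, 204 after 25% attrition and a target of 210. The last step is justified in these words: "To further ensure adequate power for subgroup and sensitivity analyses, and to allow for potential uneven group sizes after attrition".

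**The concern.** The calculation and the primary analysis test different hypotheses in different models. The interaction test has 4 degrees of freedom before the nonsphericity correction. It treats baseline as a response and asks whether any arm's trajectory over three visits differs from any other's. The primary analysis asks two single-degree-of-freedom questions at one visit, with baseline as a covariate. Power for the first says nothing direct about power for the second, and the document gives no power figure for the second.

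What is at stake is how the result is read. If Plyo-HIIT fails to separate from SF or HE, readers will take that as evidence against an effect from a trial with 90% power. If the true power is well under one half, such a result is the more likely outcome even when the assumed effect is real. The subgroup statement invites the same misreading on smaller samples.

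**Working it through.** **Inputs, all from the sample size section unless noted.** d = 0.2/0.45 = 0.444, stated as 0.44; f = 0.22; alpha 0.01; power 90%; correlation r = 0.2; epsilon = 0.70; 3 groups and 3 measurements; 153 evaluable (51 per arm); 25% attrition; target 210 (70 per arm). Expected evaluable at the target: 210 × 0.75 / 3 = 52.5 per arm. The contrasts and baseline adjustment are from the statistical analysis section. Two-sided testing is assumed.

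**1. Reproduce the plan's figure.** For the within-between interaction:

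- noncentrality λ = f² × N × m × ε / (1 − r) = 0.0484 × 153 × 3 × 0.70 / 0.80 = 19.44
- df1 = (3 − 1)(3 − 1) × 0.70 = 2.8; df2 = (153 − 3)(3 − 1) × 0.70 = 210
- power at alpha 0.01 = 0.9004 at N = 153, and 0.898 at N = 152
- 153 / 0.75 = 204

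So 153 and 204 are correct for the interaction test.

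**2. Power of one week-16 contrast.** With baseline adjustment the residual SD shrinks by √(1 − r²), so d_eff = 0.44 / √(1 − 0.04) = 0.449. Noncentrality is d_eff × √(n/2), and power comes from the noncentral t with 2n − 2 df.

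| Evaluable per arm | Noncentrality | Critical t | Power |
|---|---|---|---|
| 51 | 2.268 | 2.626 | 36.5% |
| 52 | 2.290 | 2.625 | 37.3% |
| 70 (no attrition) | 2.657 | 2.612 | 52.0% |

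Without baseline adjustment, 52 per arm gives 35.6%.

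**3. Number needed for 90%.** The same formula gives 150 evaluable per arm with r = 0.2, and 156 unadjusted. That is 450 to 468 evaluable in total, or 600 to 624 randomized at 25% attrition.

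**4. Detectable difference at 90% power, unadjusted.** 0.77 SD at 52 per arm; 0.66 SD at 70 per arm.

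**5. Sensitivity to the baseline correlation (52 per arm, alpha 0.01).**

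| r | Power |
|---|---|
| 0.2 | 37% |
| 0.5 | 49% |
| 0.8 | 86% |
| about 0.82 | 90% |

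**6. Sensitivity to alpha (r = 0.2, 51 to 52 per arm).** Alpha 0.05 gives 61% to 62%, and 75% with all 70 per arm. Alpha 0.005 gives 28% to 29%.

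**7. Both contrasts.** The two share the Plyo-HIIT arm, so their correlation is 0.5. If d = 0.44 holds against both SF and HE, the chance that both reach 0.01 is 21% to 22% at 51 to 52 per arm and about 36% at 70.

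**8. Subgroups.** Going from 204 to 210 adds 6 children, 2 per arm, or 2 × 0.75 = 1.5 per arm after attrition. As an illustration, a subgroup of half the evaluable sample (26 per arm) has 15% to 16% power for one contrast at d = 0.44 and alpha 0.01.

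**The case against.** The strongest reply is that the choice of test is not the only cause, and perhaps not the main one. The value entered in the calculation was f = 0.22 for the interaction, obtained as d/2, which is a two-group conversion. If only the Plyo-HIIT arm departs by δ SD at week 16 (or at weeks 16 and 42), the interaction f is 2δ/9. Then f = 0.22 corresponds to δ = 0.22 × 9/2 = 0.99 SD, for which one week-16 contrast at 51 per arm would have about 99% power. Conversely, δ = 0.44 gives f = 0.098, and the omnibus test has only about 16% power at N = 153. This is correct, and the conversion should be named in the correction. It does not rescue the 90%: the effect the plan justifies is d = 0.44, and at that effect neither test comes near 90%.

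Other points stand in part:

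- The plan calls r = 0.2 conservative and chose it for intervals that run to week 42. MRI-derived MFR may correlate more strongly with its own baseline over 16 weeks, so 37% is one point in a wide range. But it is the plan's only stated value, and about 0.82 would be needed for 90% at 52 per arm.
- The document does not say whether 0.45 is a cross-sectional SD or an SD of change. The adjusted figures take it as cross-sectional. On that reading an unadjusted change-score comparison at r = 0.2 would have about 21%. If 0.45 is an SD of change, the unadjusted 35% to 36% applies.
- The statistical analysis section refers to an adjustment that the sample size section does not describe. Alpha 0.01 is the natural reading; 0.05 raises power only to 61% to 62% at 51 to 52 per arm.
- No rule requires both contrasts to succeed, and the plan does not claim d = 0.44 against the active SF arm. The joint figure is conditional on both.
- Rounding to 210 was also meant to cover uneven group sizes, and no subgroup is specified. The subgroup figure is therefore illustrative.

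None of this affects the validity of the estimates or the error rate. It affects what the document says the trial can detect.

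**Conclusion.** Wrong as written. The sample size section names the week-16 difference as the primary endpoint and then attaches to it a 90% figure that belongs to another test. On the plan's own d, alpha and correlation, one primary comparison has about 37% power at the expected evaluable number and 52% with no attrition. At r = 0.2, neither alpha 0.01 nor 0.05, with anywhere from 51 to 70 per arm, reaches 90%. The figures assume two-sided tests, alpha 0.01 for each contrast, 0.45 as the SD of the week-16 measurement, and the proxy effect applying to MFR against each comparator. A high baseline correlation could lift power substantially, but the document neither states nor supports one. The claim of adequate subgroup power has no basis in two extra children per arm.

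**What to change.** In the sample size section, state the power or, better, the detectable difference for the planned analysis: a baseline-adjusted pairwise difference in MFR at week 16, at the alpha that will be used for each contrast, with about 52 evaluable children per arm. The existing calculation can stay as a dated record of how 210 was reached, provided it is labelled as applying to the omnibus interaction and the d-to-f conversion is acknowledged.

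The intervention is complete and completed assessments are being cleaned. Where week-16 MFR values are available, their SD and their correlation with baseline can be estimated with the arms pooled and unlabelled. These can then feed the detectable-difference statement without unblinding. If they are not available, give the range over r = 0.2 to 0.8.

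Delete the statement that rounding to 210 secures power for subgroup analyses. Do not add participants: recruitment has closed.

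The cost is a rewritten paragraph and one arm-blind calculation, preferably dated before the outcome analysis. Unless the observed correlation proves high, the stated power will be less favourable.
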